#### Sample size determination and accrual plan

3.6.2

Although this is a descriptive cohort study, a formal sample size calculation was performed for a secondary objective of particular significance: the development of a multivariable prediction model for in-hospital mortality. In accordance with the widely accepted criterion of a minimum of 10 events per predictor variable for logistic regression, and anticipating up to 10 potential predictors, a minimum of 100 mortality events is required. Utilizing a conservative estimated mortality rate of 12.6% as derived from previous studies, it is estimated that a total cohort of at least 794 patients would be required to achieve the desired statistical power. To account for potential incomplete data and to ensure adequate power for other secondary analyses, the target sample size is set at 1,000 patients.

The enrollment target is supported by historical annual NICU admissions across the nine high-volume tertiary centers and by pilot accrual data from the coordinating center. Together, these data indicate feasibility within the planned four-year recruitment window (2025–2028). The enrollment-monitoring framework that will be implemented includes quarterly accrual reviews and formal feasibility assessments at 12 and 24 months. In the event that accrual falls below pre-defined thresholds, pre-specified contingency measures are to be enacted. The following measures are to be implemented: activation of up to 1–3 pre-identified tertiary centers in Shenzhen, Guangdong Province; temporary augmentation of research-coordinator full-time equivalents at underperforming sites to improve case ascertainment and data capture; and structured extension of the recruitment period, subject to steering-committee and ethics-committee approval. These measures are intended to ensure the viability of the study while maintaining methodological rigor.

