##### Outcome-specific assessments

3.8.3.2

Neurodevelopmental Impairment (NDI): NDI will be defined as the presence of one or more of the following at 36 months corrected age: (1) a score <85 on any of the cognitive, language, or motor composite scales of the Bayley Scales of Infant and Toddler Development, Fourth Edition (BSID-IV); (2) a diagnosis of cerebral palsy; or (3) severe hearing or vision impairment (bilateral deafness requiring aids or blindness) (34). To capture developmental trajectories, assessments will be performed longitudinally: the Hammersmith Infant Neurological Examination (HINE) will be used at 6 and 12 months, while both the Griffiths Developmental Scales-Chinese (GDS-C) and the BSID-IV will be administered at 24 and 36 months. Audiovisual evaluations will follow the Chinese High-Risk Infant Follow-Up Protocol, including auditory brainstem response (ABR) and visual evoked potential (VEP) testing at 6–12 months and behavioral audiometry and ophthalmologic examinations at 24 and 36 months.Severe Respiratory Morbidity (SRM): SRM is defined by the need for tracheostomy, prolonged hospitalization for respiratory issues beyond 50 weeks postmenstrual age, or the requirement for supplemental oxygen, respiratory support, or respiratory monitoring, or multiple rehospitalizations for respiratory causes (35). Pulmonary function will be assessed using tidal respiratory analysis (36, 37), which evaluates parameters such as tidal volume, inspiratory/expiratory ratio, and peak tidal expiratory flow.Growth Restriction: At each visit, weight, length, and head circumference will be measured and plotted on WHO growth charts for term infants and the Fenton growth charts for preterm infants. Growth restriction will be defined as weight or length below the 10th percentile for corrected age and sex.

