### Post-discharge follow-up outcomes

4.2

Primary follow-up outcome: survival status at 36 months corrected age.Secondary follow-up outcomes: NDI, SRM, growth restriction, and loss to follow-up rates (evaluated at the 24- and 36-month assessments).

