### Statistical analysis plan

6.1

Continuous variables will be summarized as mean ± standard deviation (SD) or median with interquartile range (IQR), depending on distribution. Categorical variables will be presented as frequencies and percentages. Group comparisons will be conducted using the student's *t*-test or Mann–Whitney *U* test for continuous variables, and the *χ*² test or Fisher's exact test for categorical variables.

Univariate logistic regression will be used to examine associations between NARDS and study outcomes. Multivariable logistic regression will then be performed to identify independent predictors. Missing data will be addressed primarily using multiple imputation by chained equations (MICE), assuming data are missing at random. Variables with excessive missingness will be excluded according to predefined thresholds, and the imputation model will be structured accordingly. Sensitivity analyses will include complete-case analysis, k-nearest neighbors (k-NN) imputation, and inverse probability weighting to evaluate the robustness of findings to loss to follow-up. A two-sided *p* < 0.05 will be considered statistically significant. All analyses and visualizations will be conducted using R software (version 4.3.3).

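### Growth and Bayley scores, measured in full, are named as outcomes only through cut-offs; adding the continuous scores to the association analyses could recover power at little cost

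*Protocol article*

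**What the plan says.** Under Post-discharge follow-up assessment (3.8.3), survivors are seen at 6, 12, 18, 24 and 36 months corrected age. Under Outcome-specific assessments (3.8.3.2), weight, length and head circumference are taken at every visit and the Bayley scales at 24 and 36 months. That section also states an aim to follow development over time, but names no outcome or model for it.

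The outcomes are defined by cuts:
- Growth: "Growth restriction will be defined as weight or length below the 10th percentile for corrected age and sex".
- NDI, Bayley part: "a score <85 on any of the cognitive, language, or motor composite scales of the Bayley Scales". NDI also counts cerebral palsy and severe hearing or vision impairment.

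The secondary follow-up outcomes in 4.2 are "NDI, SRM, growth restriction, and loss to follow-up rates (evaluated at the 24- and 36-month assessments"). Section 6.2 uses the same labels as long-term prediction targets. For associations, 6.1 says "Univariate logistic regression will be used to examine associations between NARDS and study outcomes", followed by multivariable logistic regression. The same section gives a t-test or Mann–Whitney test for continuous variables in general, without linking either to growth or Bayley scores.

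**The concern.** A label that records only which side of a cut a child falls on discards how far from the cut the child lies. Long-term outcome is one of the strengths the Discussion claims for this cohort, and 3.8.3 counts NDI and growth restriction among its primary long-term outcomes (4.2 lists them as secondary). Cohort size was set for in-hospital mortality, so the long-term analyses must work with whatever survivors return. An association of severity, aetiology or treatment with growth or development could be missed on the label and visible in the same children's scores. Head circumference is measured at each visit but enters no named outcome.

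**Working it through.** **The plan's own figure.** Section 3.6.2 applies a rule of ten events for each predictor: "anticipating up to 10 potential predictors, a minimum of 100 mortality events is required". With 12.6% mortality, 10 × 10 / 0.126 = 793.7, rounded up to 794. This reproduces, but it concerns in-hospital death. No power is stated for growth or NDI.

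**Inputs from the article.** Target 1,000; mortality 12.6%; two-sided 5% level (6.1). Survivors: 1,000 × (1 − 0.126) = 874.

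**Assumptions (not in the article).** Share of survivors seen: 100%, 80% or 60%, giving 874, 699 or 524. Two equal groups. Normal scores, with the exposed group shifted by the same amount on every scale. Weight–length correlation 0.7; Bayley inter-scale correlation 0.6; Bayley mean 100 and SD 15, so that 85 is −1 SD. The unexposed mean is at the reference norm, or 0.5 SD below it.

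**Formulas.** With n per group and shift d in SD units:
- One continuous score: power = Φ(d/√(2/n) − 1.96).
- Label: p₁ and p₂ are the multivariate-normal probabilities that any scale lies below its cut. Power = Φ((|p₂ − p₁| − 1.96·s₀)/s₁), where s₀ and s₁ are the standard errors of the difference under a common rate and under separate rates.

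**Base case: 699 seen (n = 349.5), d = 0.25, mean at norm.**
- Continuous: 0.25/0.0757 = 3.305; Φ(3.305 − 1.96) = 91%.
- Growth label: 15.3% vs 22.3%; s₀ = 0.0296, s₁ = 0.0295; Φ((0.0701 − 0.0579)/0.0295) = 66%.
- Bayley part of NDI: 30.3% vs 40.5%; s₀ = 0.0362, s₁ = 0.0360; Φ((0.1017 − 0.0709)/0.0360) = 80%.

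**Range** (power in %, loss against one continuous score in points):

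| Seen | Shift, SD | Continuous | Growth label (loss) | Bayley label (loss) | Losses if mean 0.5 SD below norm: growth, Bayley |
|---|---|---|---|---|---|
| 524 | 0.20 | 63 | 37 (26) | 49 (14) | 17, 11 |
| 524 | 0.25 | 82 | 54 (28) | 68 (13) | 17, 11 |
| 699 | 0.20 | 75 | 47 (28) | 61 (14) | 18, 11 |
| 699 | 0.25 | 91 | 66 (25) | 80 (11) | 14, 9 |
| 874 | 0.20 | 84 | 56 (28) | 71 (13) | 17, 10 |
| 874 | 0.25 | 96 | 76 (20) | 88 (8) | 10, 6 |

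**Where the loss shrinks.**
- Shift of 0.40 SD, equal groups: at most 8 points for growth and 2 for the Bayley part (524 seen), because power nears its ceiling.
- Harm confined to 10% of exposed children, 2 SD each (699 seen): growth label 67%, continuous score 68%.
- NDI with its other components added to the base case, at assumed independent rates: 3% vs 5% gives 86%, 3% vs 6% gives 89% and 5% vs 10% gives 93%, against 91% for one composite.

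**Why the direction is general for a uniform shift.** A single cut of a normal score at proportion p keeps φ(z)²/[p(1 − p)] of the information: 34% at the 10th percentile and 44% at −1 SD. The any-scale rules pool several scales and so lose less than a single cut, as the table shows. Under the assumed correlations they would also label about 15% (growth) and 30% (Bayley) of a reference population.

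**The case against.** The strongest reply is that the article never says the scores will be analysed only as cuts. It has a general provision for continuous variables and an aim to follow development over time. Its logistic sentence cannot be a strict rule for every outcome, because ventilator-free days and duration of ventilation are listed outcomes too. A reader might infer that continuous analysis is ruled out; the text does not support that, and the full analysis plan is not shown. What remains is that no continuous growth or Bayley outcome is named. The t-test and Mann–Whitney provision is unadjusted, while 6.5 calls for adjusted models and the only regression named for associations is logistic.

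Three further replies stand:
- The models in 6.2 are classifiers judged by AUROC, sensitivity and specificity, so binary targets are right there.
- NDI is more than a Bayley cut. Cerebral palsy and sensory impairment are categorical, and a child who cannot complete the Bayley can still count as NDI through them but would drop out of a score model.
- The size of any gain depends on how harm is distributed, as the last scenarios in the working show.

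It is also uncertain whether growth before 24 months is left out: the 24- and 36-month wording in 4.2 may qualify only loss to follow-up.

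**Conclusion.** The point holds as a worthwhile, inexpensive improvement. The growth and developmental-score outcomes named are cut-based labels paired with logistic regression, although the scores behind them are collected in full. For a uniform shift of 0.20 to 0.25 SD, with 524 to 874 survivors seen, equal groups and the stated correlations, the loss is roughly 10 to 28 points of power for growth and 6 to 14 for the Bayley part of NDI. The lower ends belong to a cohort already 0.5 SD below norm with every survivor seen. The loss is small at 0.4 SD or more in equal groups, and can disappear for growth under subgroup harm and for NDI when its other components differ.

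A reader might infer that a power claim in the article is wrong, or that the labels should be demoted. Neither follows. No effect size or power is stated for these analyses, and the labels are legitimate clinical outcomes.

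**What to change.** Keep NDI and growth restriction as the clinical outcomes and as the targets of the 6.2 prediction models. In 4.2 and 6.1, add continuous outcomes for the adjusted association and comparative analyses:
- weight, length and head-circumference z-scores in a mixed model over the 6, 12, 18, 24 and 36 month visits;
- the three Bayley composites by linear or mixed model at 24 and 36 months.

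Report these beside the logistic results.

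The cost is wording and a little more analysis, since every score is already collected. Mean differences are less directly clinical than proportions, which is why the labels stay. Children who cannot complete the Bayley drop out of the score model, so report their number and keep them in NDI.

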#### Data on confounding factors and NARDS etiology

3.8.4

Recognizing the significance of confounding factors, particularly in the premature infant population, the data will be stored in the “Perinatal Cloud Database” (https://www.perinatalcloud.com/). This system, developed by the study's principal investigator (ZY), utilizes an advanced online Case Report Form (CRF) designed to comprehensively capture potential confounders. Data collected will include detailed maternal history, gestational age, birth weight, and sex, along with significant neonatal comorbidities such as hsPDA, IVH, sepsis, and NEC. A comprehensive record of all treatment data will also be kept, including details regarding surfactant administration, ventilation strategies, and inotrope use. Further details about the database can be found in the Supplementary Material.

Furthermore, to address the underlying causes, each NARDS case will be classified as either “direct” (triggered by a primary pulmonary insult, such as pneumonia or meconium aspiration) or “indirect” (triggered by an extrapulmonary systemic insult, such as sepsis or perinatal asphyxia). This classification, which includes specific criteria for diagnoses like pneumonia (direct) or sepsis-associated NARDS (indirect), will be determined by the site investigator and reviewed for consistency by a central adjudication committee.

## Outcomes

4

### In-hospital outcomes

4.1

Primary in-hospital outcome: composite of mortality or requirement for ECMO within 28 days of NARDS diagnosis.Secondary in-hospital outcomes include: 28-day mortality; 28-day ventilator-free days; duration of invasive mechanical ventilation; incidence of BPD, severe pulmonary hemorrhage, and air leak syndromes; and incidence of significant non-pulmonary organ dysfunction, including hsPDA, NEC (stage ≥ II), and severe IVH (grade ≥ III).

### Post-discharge follow-up outcomes

4.2

Primary follow-up outcome: survival status at 36 months corrected age.Secondary follow-up outcomes: NDI, SRM, growth restriction, and loss to follow-up rates (evaluated at the 24- and 36-month assessments).

### Biomarker and predictive modeling outcomes

4.3

The primary outcomes related to the multi-omics biomarker analysis are:
The identification and validation of a proteomic and/or metabolomic signature, derived from baseline (within 24 h of diagnosis) plasma/serum samples, that demonstrates high accuracy [defined as an Area Under the Receiver Operating Characteristic Curve (AUROC) > 0.85] for predicting the development of severe NARDS (OI ≥ 16) within 72 h of diagnosisThe discovery of novel genetic variants *via* a Genome-Wide Association Study (GWAS) that are significantly associated with susceptibility to NARDS and/or in-hospital mortality.

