#### Inclusion and exclusion criteria

3.6.1

Neonates will be enrolled consecutively upon meeting the full set of Montreux criteria for the diagnosis of NARDS during hospitalization. This cohort will include infants of all gestational ages, including premature infants, provided their respiratory distress meets all five Montreux criteria. These criteria include: (1) an acute onset of symptoms within one week following a known or suspected clinical insult; (2) exclusion of respiratory distress attributable to neonatal respiratory distress syndrome (NRDS), transient tachypnoea of the newborn (TTN), or congenital anomalies; (3) radiological evidence of bilateral, diffuse irregularities, including reduced translucency or opacities, that cannot be explained by conditions such as pleural effusion, atelectasis, NRDS, TTN, or congenital anomalies; (4) absence of congenital heart disease as the cause of pulmonary oedema, with echocardiographic confirmation required to verify the origin of the oedema; and (5) the presence of an oxygenation deficit, categorized by the OI as mild (4 ≤ OI < 8), moderate (8 ≤ OI < 16), or severe (OI ≥ 16). All five criteria must be fulfilled for diagnosis.

Exclusion criteria include: (1) respiratory distress due to primary surfactant deficiency (e.g., hyaline membrane disease), TTN, or congenital lung malformations; (2) congenital heart disease resulting in pulmonary oedema; (3) known genetic syndromes or chromosomal abnormalities; (4) data that did not conform to the Montreux criteria or cases with unavailable outcome data; and (5) abandonment or death occurring within 24 h of birth.

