#### Clinical data and key variable definitions

3.8.1

Demographic characteristics, baseline information, and follow-up data will be systematically recorded following admission and discharge. During hospitalization, data collected will include physical examination findings, neonatal critical illness scores, diagnoses, complications, biochemical parameters, pathogen cultures, imaging results, and treatments administered. Post-hospitalization follow-up assessments will be conducted at designated time points: on day 1 (within 24 h of NARDS diagnosis), during the acute exacerbation phase (defined as the moment when the OI reaches its peak), and on day 28 (or the final day of hospitalization if shorter than 28 days). For patients who succumb to their condition or require ECMO, data will also be gathered 24 h prior to death or the initiation of ECMO. Supplementary data, including hospitalization duration and associated costs, will also be documented.

Key clinical variables were standardized to ensure consistency in reporting:

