### Machine learning and predictive modeling

6.2

Beyond conventional regression, predictive modeling will employ a suite of algorithms, including penalized logistic regression (Elastic Net), decision trees, random forests, gradient boosting machines, support vector machines, and artificial neural networks. Two primary prediction tasks will be addressed: Early identification of neonates at risk of severe NARDS (OI > 16 within 72 h of diagnosis); Long-term prognosis (mortality, NDI, SRM, or growth restriction at the 24- and 36-month corrected age). Candidate predictors will be selected based on clinical relevance and temporal availability (within 24 h for early warning models; within 7 days for prognostic models). Feature selection and regularization will primarily use Elastic Net. To identify novel NARDS endotypes, Integrative Multi-Omics Factor Analysis (MOFA) or similar unsupervised data integration approaches [e.g., sparse Partial Least Squares Discriminant Analysis (sPLS-DA)] will be employed to identify latent factors and co-varying molecular pathways across omics layers. These integrated molecular signatures will subsequently serve as input features for downstream machine learning models (e.g., Random Forest) to construct highly discriminative and biologically informed predictive classifiers.

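### The AUROC for severe NARDS within 72 h mixes detection of current severity with prediction, because predictor and outcome windows overlap and no at-risk set is stated

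*Protocol article*

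**What the plan says.** - **Eligibility (Section 3.6.1).** The oxygenation criterion admits all grades: "categorized by the OI as mild (4 ≤ OI < 8), moderate (8 ≤ OI < 16), or severe (OI ≥ 16". An infant can be severe at the moment of diagnosis and be enrolled.
- **Primary biomarker outcome (Section 4.3).** The signature is "derived from baseline (within 24 h of diagnosis) plasma/serum samples". It must reach an AUROC above 0.85 "for predicting the development of severe NARDS", defined as OI ≥ 16 in the 72 h after diagnosis.
- **Early-warning task (Section 6.2).** The target is "Early identification of neonates at risk of severe NARDS (OI > 16 within 72 h of diagnosis". Candidate predictors are taken "within 24 h for early warning models; within 7 days for prognostic models".
- **Abstract, Results.** The 0.85 threshold is also attached to a model that joins early clinical variables to omics markers, with severe disease given as OI ≥ 16.
- **In-hospital data points (Section 3.8.1).** Data are collected on day 1, "during the acute exacerbation phase (defined as the moment when the OI reaches its peak", on day 28 or the last hospital day, and before death or ECMO.

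No section says that the prediction analysis is limited to infants below OI 16 at diagnosis or at sampling, or that outcome counting starts after the predictors are fixed.

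**The concern.** A prediction target needs infants who are still free of the event when the predictors are measured. Here both clocks start at diagnosis, so the predictor window is the first 24 of the 72 outcome hours. Two groups can then be counted as predicted although the event came before or with the measurement:

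1. infants already at OI ≥ 16 at diagnosis, if they are kept in the analysis;
2. infants who cross 16 after diagnosis but before their sample is drawn.

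At stake is the meaning of the success criterion for the primary biomarker outcome. An AUROC above 0.85 would be read as early warning, when part of it would be recognition of a state that the bedside team already knows. The validation in Sections 6.3 and 6.4 (70/30 split, cross-validation, bootstrap) would not reveal this, because the same outcome definition is used in every subset.

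**Working it through.** **Plan's own figure.** The article gives no derivation for the 0.85 threshold, so there is nothing to reproduce. The only sample-size calculation (100 / 0.126 = 793.7, rounded up to 794) concerns in-hospital mortality and does not bear on this point.

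**Step 1: does the problem survive a new-onset reading?** Take an infant at OI 12 at diagnosis who crosses 16 at hour 6 and is sampled at hour 20. The infant developed severe disease within 72 h, and the sample lies within 24 h. Both stated conditions are met, yet the sample follows the event. So reading the target as new onset removes group 1 but not group 2.

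**Step 2: how much can it inflate the AUROC?** Define:

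- w = share of 72 h cases already at OI ≥ 16 when predictors are measured (not in the article; assumed);
- A_prev = AUROC for those cases against non-cases;
- A_inc = AUROC for later-onset cases against non-cases, which is the real predictive ability.

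The overall AUROC is a weighted mean over cases:

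AUROC = w × A_prev + (1 − w) × A_inc

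With perfect recognition of current severity (A_prev = 1) and no prediction of later onset (A_inc = 0.50):

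| w | AUROC |
|---|---|
| 0 | 0.50 |
| 0.3 | 0.65 |
| 0.5 | 0.75 |
| 0.7 | 0.85 |
| 0.8 | 0.90 |
| 0.9 | 0.95 |

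A simulation with 1,000 infants and 300 assumed cases (300 replicates) agrees: 0.751 at w = 0.5 and 0.850 at w = 0.7, with about 0.50 for the later-onset cases alone.

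**Step 3: what share is needed to pass 0.85?** Solve for w:

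w > (0.85 − A_inc) / (A_prev − A_inc)

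| A_prev | A_inc = 0.50 | A_inc = 0.70 |
|---|---|---|
| 1.00 | 0.35/0.50 = 0.70 | 0.15/0.30 = 0.50 |
| 0.95 | 0.35/0.45 = 0.778 | 0.15/0.25 = 0.60 |
| 0.90 | 0.35/0.40 = 0.875 | 0.15/0.20 = 0.75 |

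With A_prev at or below 0.85, and A_inc lower still, the threshold cannot be passed.

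**Step 4: what does the overlap alone give?** If no case is severe at diagnosis, onset is uniform over 72 h and all samples are drawn at 24 h, then w = 24/72 = 0.33 and the AUROC is 0.5 + 0.5 × 0.33 = 0.67. If a share d of cases is severe at diagnosis, w = d + (1 − d)/3. Reaching w = 0.70 needs d = 0.55.

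**Step 5: the same in terms of the cohort.** Let s be the share of all infants severe at diagnosis and p the share of the rest who cross within 72 h. For a marker that only flags severity at diagnosis, w = s / (s + (1 − s)p) and AUROC = (1 + w)/2.

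- s = 0.30, p = 0.15: w = 0.30/0.405 = 0.741, AUROC 0.870
- s = 0.40, p = 0.30: w = 0.40/0.58 = 0.690, AUROC 0.845
- s = 0.15, p = 0.30: w = 0.15/0.405 = 0.370, AUROC 0.685

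Both s and p are assumptions, and the result falls on either side of 0.85 within plausible-looking ranges.

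**Step 6: cut-off.** The Abstract and Sections 3.6.1 and 4.3 use OI ≥ 16; Section 6.2 uses OI > 16. An infant at exactly 16 is a case in one section and not in the other.

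**The case against.** **The wording points to new onset.** Section 4.3 speaks of development and Section 6.2 of infants at risk. This stands: a reader might infer that the plan counts already-severe infants as cases, but the article does not say so. It is silent. Step 1 shows that the overlap remains under the new-onset reading.

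**An article may leave the at-risk set to the full analysis plan.** Fair for detail in general. Here, though, the article itself states the outcome window, the predictor window and the success threshold, and the windows overlap as stated.

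**An AUROC above 0.85 with no predictive ability is not shown.** This stands as a limit. A reader might infer that the criterion can be met simply by reading the admission OI. For the plasma or serum signature of Section 4.3 that does not follow: it would have to recognise current severity through biology, and at A_prev = 0.90 it would need 87.5% of cases already severe. The argument is stronger for the combined model in the Abstract, because baseline data in Table 1 include blood gases and respiratory support settings. Even so, OI is nowhere named as a candidate predictor.

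**The 7-day prognostic model.** A reader might infer that deaths before day 7 are counted against predictors collected up to day 7. The article does not say that such infants enter the model, and its targets are set at 24 and 36 months. A clarifying sentence is enough.

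**Outcome capture.** A reader might infer that 72 h status is not recorded. The scheduled points leave it open only for infants below 16 on day 1 whose peak of 16 or more falls after 72 h. The case report form is not shown and may settle even those.

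**Reach.** The study's primary objective and its primary in-hospital outcome are untouched, and biobanking is a voluntary sub-study.

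**Conclusion.** The concern holds in a limited form. As stated, the windows allow samples drawn after the event to count as prediction, and no restriction to infants below OI 16 is given. The reported AUROC would therefore mix detection with prediction.

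The size depends on w, which the article does not give. With perfect detection and no prediction, half of the cases already severe yields 0.75, and passing 0.85 needs more than about 70%. Less perfect detection needs a larger share; some real prediction (A_inc = 0.70) lowers the requirement to 50% under perfect detection. The documents do not support saying that the threshold will be met without predictive ability, only that it could be under these conditions, and that any w above zero raises the AUROC whenever current severity is easier to recognise than later onset.

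The difference in cut-off is a plain inconsistency. On a continuous index its numerical effect is likely small.

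**What to change.** Change the wording of Sections 4.3 and 6.2 as follows.

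- **At-risk set.** Restrict the prediction analysis to infants whose OI has stayed below 16 up to a landmark: the time of the baseline sample, at latest 24 h after diagnosis. Use no predictor measured after the landmark.
- **Event.** Count the first OI ≥ 16 from the landmark to 72 h.
- **Death and ECMO.** State how either one before 72 h is handled. Adding them to the event would create a different endpoint, so that is a choice to be made openly and not a correction.
- **Already-severe infants.** Report them separately.
- **Cut-off.** Use one form in both sections.
- **Reference.** Report the model's AUROC beside that of OI at the landmark alone.
- **7-day model.** State that it applies to infants alive at day 7.
- **Data.** Confirm that the case report form dates the first OI ≥ 16 within 72 h. If it does not, add that field while recruitment is open.

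The cost is protocol or analysis-plan wording and possibly one field taken from routine charts. The restricted analysis will have fewer events, and its AUROC will probably be lower, but it will measure prediction.

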#### Epidemiological and clinical characterization

2.2.1

To evaluate the prognostic performance and clinical utility of the Montreux NARDS definition within the Shenzhen cohort. This involves assessing its association with mortality, severe morbidity, and long-term neurodevelopmental impairment (NDI), thereby establishing a robust framework for subsequent deep phenotype analysis.To determine the incidence, disease burden, and clinical characteristics of NARDS in participating NICUs, and to describe the short-term mortality and morbidity of affected infants.To characterize the clinical trajectories of NARDS, including the time course from the inciting insult to key endpoints such as severe disease, the requirement for extracorporeal membrane oxygenation (ECMO), or death, and to analyze mortality patterns over a three-year follow-up period.

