#### Biomarker discovery and validation

2.2.3

To discover and validate novel biomarkers for NARDS by linking our longitudinal biobank to clinical outcomes. This includes:
Identifying predictive proteomic and metabolomic signatures for severe NARDS (sNARDS) using longitudinally collected plasma/serum samples.Characterizing the local inflammatory milieu through transcriptomic analysis of tracheal aspirates.Performing a genome-wide association study (GWAS) using genomic DNA from blood to identify genetic variants associated with NARDS susceptibility and severity.

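### The cohort contains only NARDS cases, so the susceptibility part of the GWAS and a regression with NARDS as the exposure cannot be estimated

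*Protocol article*

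**What the plan says.** Enrolment is fixed in section 3.6.1 (Inclusion and exclusion criteria): "Neonates will be enrolled consecutively upon meeting the full set of Montreux criteria for the diagnosis of NARDS during hospitalization", and "All five criteria must be fulfilled for diagnosis". The exclusion list in the same section removes data that do not meet the Montreux criteria. The legend of Figure 2 describes recruitment as recruitment of diagnosed infants only. Section 3.6.2 sets the target at 1,000 such patients.

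The genetic aims appear in two places:

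- Section 2.2.3 (Biomarker discovery and validation) plans a GWAS on DNA from blood to "identify genetic variants associated with NARDS susceptibility and severity".
- Section 4.3 (Biomarker and predictive modeling outcomes) counts among the primary multi-omics outcomes variants "that are significantly associated with susceptibility to NARDS and/or in-hospital mortality".

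Section 6.1 (Statistical analysis plan) opens its regression plan with this sentence: "Univariate logistic regression will be used to examine associations between NARDS and study outcomes". It closes with a general rule that a two-sided p below "0.05 will be considered statistically significant". Sections 6.2 to 6.5 describe no GWAS method and no other threshold.

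**The concern.** Susceptibility asks why one infant develops NARDS and another does not. Answering it requires genotypes from infants without NARDS, or some substitute for them. The design, participant, biospecimen and statistics sections of the article describe none. A named outcome of the biomarker programme therefore promises a contrast that the sampled population does not contain.

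The regression in section 6.1 has the same problem. If every participant has NARDS, an association between having NARDS and any outcome cannot be measured inside the cohort.

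Two smaller matters come with this. The two GWAS statements pair susceptibility with different second traits, severity in 2.2.3 and in-hospital mortality in 4.3, so the trait to be analysed is not settled. And section 4.3 makes success depend on significance, while the only significance rule printed in the article would be unusable for a genome-wide scan if someone applied it there.

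**Working it through.** **The plan's own figure.** Section 3.6.2 uses 10 events per predictor, 10 predictors and 12.6% mortality. Required events are 10 × 10 = 100, and 100 / 0.126 = 793.65, rounded up to 794. The stated 794 is reproduced. It sizes the in-hospital mortality model only and does not address the GWAS.

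**Susceptibility contrast.** The allelic odds ratio is (a/b) / (c/d), where a and b are the counts of the two alleles in cases and c and d the counts in controls.

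- Cases: a + b = 2 × 1,000 = 2,000 alleles at the target size.
- Controls: c + d = 2 × 0 = 0 alleles.
- c/d is 0/0, so the odds ratio is undefined at any sample size.

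**Within-case contrasts.** At 12.6% mortality, 1,000 infants give 126 deaths and 874 survivors, that is 2 × 126 = 252 alleles against 2 × 874 = 1,748. Both groups are non-empty, so an odds ratio exists. These counts assume that every family consents to the biobank. Section 3.8.2 makes it a voluntary sub-study with separate consent, so they are upper limits for this mortality rate and cohort size. Severity can also be estimated, because section 3.6.1 assigns every infant an OI grade (4 to below 8, 8 to below 16, 16 or more). The article gives no expected split between grades, so no count is shown.

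**Regression in section 6.1.** With NARDS = 1 for everyone, the model is logit(p) = β0 + β1 × 1 = β0 + β1. The design matrix has two identical columns of ones and rank 1 of 2. Taking death as the outcome with 126 of 1,000, the data fix only the sum β0 + β1 = ln(126/874) ≈ −1.94. Every split between intercept and slope fits equally well, so β1 has no estimate.

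**The p < 0.05 rule, if it were applied to a genome-wide scan.** The article gives no number of variants, so the number of independent tests m is an assumption. With no true association, expected false positives are 0.05 × m, and the Bonferroni level is 0.05 / m.

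| Assumed m | Expected false positives at 0.05 | 0.05 / m |
|---|---|---|
| 100,000 | 5,000 | 5e-7 |
| 1,000,000 | 50,000 | 5e-8 |
| 5,000,000 | 250,000 | 1e-8 |

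**The case against.** **The outcome in 4.3 is joined by and/or.** The mortality alternative can be analysed within cases, and so can severity in 2.2.3. This stands. A reader might infer that the whole GWAS outcome fails, but the documents do not support that: only the susceptibility part fails.

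**It is primary only within the multi-omics component.** This also stands. The main in-hospital and follow-up outcomes in sections 4.1 and 4.2 do not depend on it.

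**Controls may be named in the full protocol or analysis plan.** An article may leave genotyping detail elsewhere. But the point does not rest on silence about a detail. The enrolment rule is printed and limits sampling to cases, and the biospecimen sections describe sampling under this cohort only. Table 1 records annual NICU admissions, but as unit totals without genotypes. A case-parent design would avoid unrelated controls, but no parental blood sampling or family-based analysis is described. If a control source does exist, one sentence naming it would settle the matter.

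**The regression sentence in 6.1 is only loose wording.** The next sentence speaks of independent predictors, so the intention may well be characteristics or severity within NARDS, which can be estimated. That is a fair reading and makes this limb a wording fix, but the text names NARDS itself as the variable.

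**The p < 0.05 rule sits with the conventional tests.** It follows t-tests, χ² tests and logistic regression and is never tied to the GWAS. A reader might infer that genome-wide results will be judged at 0.05. The article does not say so, and the threshold may properly sit in the analysis plan. Nor does the rule govern the omics models, which section 6.4 judges by AUROC and calibration metrics in the validation set. Only a clarification is warranted.

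**Section 2.2.1 may look untestable too.** It aims "To evaluate the prognostic performance and clinical utility of the Montreux NARDS definition within the Shenzhen cohort", and nobody in the cohort fails the definition. But the definition includes the OI grades, and comparing outcomes across grades can serve that aim, so no defect is claimed there.

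**Conclusion.** The point holds in a limited form. The susceptibility part of the GWAS objective in 2.2.3 and of the multi-omics outcome in 4.3 cannot be estimated from a case-only cohort: 1,000 cases, 0 controls, no odds ratio. As worded, the regression on NARDS in 6.1 has no estimable coefficient. The severity and mortality parts of the GWAS remain estimable, but the two sections should agree on which is meant.

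This rests on one assumption: that no control genotype source exists beyond what the article describes. The false-positive range (5,000 to 250,000) rests on assumed numbers of tests and on a use of the 0.05 rule that the article does not state, so it supports a clarification and nothing more. The correction should be made before the genetic analysis is fixed, but it falls short of a must-fix.

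**What to change.** 1. In 2.2.3 and 4.3, delete susceptibility and state the same within-case GWAS trait or traits in both places: severity, in-hospital mortality, or both. Alternatively, keep susceptibility and name an existing ancestry-matched control genotype set.
2. In 6.1, replace NARDS as the exposure with Montreux severity grade and direct/indirect etiology. Both are already recorded under sections 3.6.1 and 3.8.4.
3. As a minor clarification in 6.1, state that the p < 0.05 rule does not apply to the GWAS, which uses a genome-wide threshold such as 5e-8.

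The cost is wording only if susceptibility is dropped, with no change to enrolment, sampling or follow-up. The price is a narrower claim, since no susceptibility finding can be promised. Keeping susceptibility means obtaining and matching an external control set.
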